#### Inclusion Criteria

The following inclusion criteria will be applied:

patients of both sexes over 18 years of age;patients attended by health care professionals of the basic health areas participating in the study;patients who give their agreement to participate in the study by signing an informed consent form;patients who have a mobile device (smartphone or tablet) compatible with the Android or iOS operating system;considered as a patient with multimorbidity based on the criteria described in the previous section.

#### Exclusion Criteria

The following exclusion criteria will be applied:

patients with sensory deficits or upper limb mobility problems that prevent them from using the app correctly, despite using the accessibility features on mobile devices;patients with persistent cognitive impairment (Pfeiffer [33] with ≥5 errors or Lobo Mini-Cognitive Test score <23 [34]) or severe mental disorder;patients with severe limitations for basic activities of daily living (Barthel Index <20 points [35]).

#### Eligibility Criteria

Meet all inclusion criteria and none of the exclusion criteria.

#### Completion Criteria and Withdrawal

A patient will be considered to have completed the study when he/she completes the postintervention evaluation. The criteria for withdrawal of a participant will be

failure to receive the complete intervention (unsolvable technical failures in the device) or by the protocol (failure to use the app);loss of compliance with the eligibility criteria during the study or withdrawal of consent to participate;inability to contact for follow-up.

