#### Diagnostic Criteria

Patients with multimorbidity and HF and complex health needs who meet the following diagnostic criteria [12] will be considered:

Be classified in clinical category A of chronic pathologies for HF that, in a situation of clinical stability, has been in grade II of the New York Heart Association (NYHA) [31], being able to be simultaneously classified, or not, in other clinical categories for having another chronic disease(s) included in these categories.Patients with at least one of the following complexity criteria [12]: extreme polypharmacy (≥10 chronically prescribed active ingredients); sociofamilial risk (Gijon scale score [32] >10 points); pressure ulcers of stage II or higher; malnutrition (body mass index <18.5 kg/m^2^); nasogastric feeding (≥3 months); 2 or more hospital admissions in the previous 12 months.

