3	The patient will come for a consultation to check compliance with the chosen objective. If necessary, a simulation test will be performed to confirm that the challenge has been met. At the end of this stage, the patient and the multidisciplinary team will agree on the second objective.			✓	✓	✓	✓							
4	Check compliance with the second objective. Perform simulation test, if required. At the end of this stage, the patient and the multidisciplinary team will agree on the third objective.						✓	✓	✓	✓				
5	Check compliance with the third objective. Perform simulation test, if required.									✓				
6	Postintervention evaluation: all health objectives were achieved by the patient and postintervention evaluation is performed										✓	✓	✓	
7	Follow-up	At 12 months after the intervention												

^a^✓: achievement record.

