**Secondary response**				
	Personal autonomy basic activities of daily living	0-100	Barthel Index [35]	Registration
	Personal autonomy instrumental activities of daily living	0-8	Lawton-Brody Index [42]	Registration
	Therapeutic adherence	0-4	Morisky-Green Adaptation Questionnaire [43] and Recipe XXI	Registration
	Vital forecast	0-30	PROFUND Index [44]	Registration
	Satisfaction with service	0-10	Satisfaction Scale	Nursing record
	Mobile health device satisfaction	1-5	Satisfaction Scale	Built-in mobile health device registration

^a^HLS-EU-Q47: 47-item European Health Literacy Questionnaire.

^b^NOC: Nursing Outcomes Classification.

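### Withdrawing patients for device failure, not using the app or losing eligibility would probably leave them without a final outcome; the app-related rule acts in one arm only and risks favouring the app

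*Protocol article*

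**What the plan says.** The section Completion Criteria and Withdrawal of the protocol article lists the reasons for withdrawing a participant. The first is "failure to receive the complete intervention (unsolvable technical failures in the device) or by the protocol (failure to use the app"). The second is "loss of compliance with the eligibility criteria during the study or withdrawal of consent to participate". The third is that the patient cannot be contacted for follow-up. The same section defines a completer: "A patient will be considered to have completed the study when he/she completes the postintervention evaluation".

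Four other places bear on these rules:

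- Description of the Intervention: only the experimental group receives the app. Controls have usual practice and, like the app group, agree three objectives.
- Exclusion Criteria: "patients with severe limitations for basic activities of daily living (Barthel Index <20 points [35"]) are excluded, as are patients beyond stated limits on two cognitive tests. Eligibility Criteria requires that no exclusion criterion is met.
- Table 3, secondary responses: "Personal autonomy basic activities of daily living", measured with the Barthel Index on 0–100.
- Data Analysis: Data Encoding: between-group and within-group tests and regression models. It names no analysis population and does not say whether withdrawn patients are followed or analysed.

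**The concern.** Device failure and non-use are listed beside withdrawn consent and lost contact, so on a plain reading they are exits from the study and not only from the app. No control patient can meet them. The patients who leave the app arm this way are unlikely to be a random subset. The Introduction links low health literacy to poorer self-management and poorer adherence to care plans, Limitations names digital illiteracy as a difficulty, and the main outcome is a health-literacy score. Patients with low expected scores may therefore leave one arm while their counterparts remain in the other, and randomisation would no longer protect the main comparison.

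The eligibility rule is a different problem. It can remove a patient because of the value of an outcome: someone who falls below Barthel 20 would be withdrawn when that decline should count as a poor result.

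Neither loss can be repaired at the analysis stage if the final assessment was never made.

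**Working it through.** **Inputs from Sample Size.** HLS-EU-Q47 mean 32.88, SD 6.10, relevant increase 10%, two-sided alpha 0.05, 118 per group, 30% loss. The printed β of .90 is read as power 0.90. Target difference: 0.10 × 32.88 = 3.288 points.

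**The plan's own figure.** n per group = 2 × [6.10 × (1.960 + 1.282) / 3.288]² = 72.3, so 73, and 73 / 0.70 gives 105 after 30% loss. The stated 118 is not reproduced. It is larger than its inputs require, and the present point does not depend on it. Because the article does not make clear whether 118 is before or after loss, power is shown below both for 118 analysed per group and for 118 × 0.70 = 82.6, so 83.

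**Assumptions (not in the documents).** A fraction f of the app arm does not use the app and has no final outcome. Non-users would score g SDs below users. The app has no true effect. All 118 controls are assessed.

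**Formulas.**
- Spurious benefit b = f × g × 6.10.
- SE = 6.10 × √[1/118 + 1/(118(1 − f))], which is 0.816, 0.842 and 0.875 for f = 10, 20 and 30%.
- Type I error = Φ(b/SE − 1.96) + Φ(−b/SE − 1.96).

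Example, f = 20% and g = 0.5: b = 0.20 × 0.5 × 6.10 = 0.61 points, b/SE = 0.61 / 0.842 = 0.724, type I error 11.2%.

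| Gap g | f = 10% | f = 20% | f = 30% |
|---|---|---|---|
| 0 | 0 points; 5.0% | 0 points; 5.0% | 0 points; 5.0% |
| 0.25 SD | 0.15; 5.4% | 0.31; 6.5% | 0.46; 8.2% |
| 0.5 SD | 0.31; 6.6% | 0.61; 11.2% | 0.92; 18.2% |

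As a share of 3.288 points, the last row is 9, 19 and 28%. Allowing for the slightly smaller SD among users moves the last two entries to 11.3% and 18.6%.

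**Eligibility rule.** No rate is given, so this is reasoning only. The rule acts in both arms. With no app effect, similar patients leave each arm and no systematic difference arises. If the app preserved function, more controls would fall below Barthel 20 and be removed, which works against the app. If the app arm declined more, the reverse holds. In every case the lowest Barthel results are missing. Read literally, the rule could also reach a patient who entered on "2 or more hospital admissions in the previous 12 months" (one of six alternative complexity criteria) and then has a good year, while readmissions are a main response. The article does not say whether that is meant.

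**Power if everyone is kept.** Assume non-users gain nothing, so the effect becomes 3.288 × (1 − f). Power = Φ(effect / [6.10 × √(2/n)] − 1.96).

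| f | Effect | n = 118 | n = 83 |
|---|---|---|---|
| 0 | 3.29 | 98.5% | 93.5% |
| 10% | 2.96 | 96.1% | 87.8% |
| 20% | 2.63 | 91.2% | 79.3% |
| 30% | 2.30 | 82.6% | 68.1% |

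**The case against.** The strongest reply is that withdrawal is not exclusion from analysis. The article never says that collected data are discarded or that the analysis is per protocol. Analysis sets are commonly left to a statistical analysis plan, which is not shown. This stands: a reader might infer that the planned comparison is users against all controls by design, and the text does not support that. It does not remove the point, because the withdrawal rule governs conduct. An analysis plan can define an intention-to-treat set, but it cannot recover assessments that were not made.

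A reader might also infer that both rules favour the app. Only the app-related rule has a likely direction. The eligibility rule is shared by the arms, and the Barthel part concerns one of six secondary responses. How strictly the cognitive limits would be applied during the study is also unclear, since Limitations says that the usual caregiver is included to deal with cognitive impairment.

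The size is open as well. Without a gap between users and non-users there is no bias. Stage 2 of Table 1 provides individual app instruction, a self-efficacy assessment and help with difficulties, and Limitations mentions digital training; these should lower non-use.

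Finally, Table 1 describes the postintervention stage as one where "all health objectives were achieved by the patient and postintervention evaluation is performed". A reader might take this to limit the assessment to successful patients, but it may only describe the expected sequence, so nothing here rests on it.

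**Conclusion.** The point holds as a flaw in a stated conduct rule. Device failure and non-use lead to withdrawal in one arm only. Patients withdrawn before the postintervention evaluation would probably have no final health-literacy score, and the likely bias is in favour of the app. Under no true effect, 118 per arm and 10–30% non-use, type I error ranges from the nominal 5% (no gap) through about 5–8% (0.25 SD) to about 7–18% (0.5 SD, spurious benefit 0.3–0.9 points). These are illustrations: the documents give neither the non-use rate nor the gap, and control losses are ignored. For the eligibility rule the conclusion is narrower: it cuts off the worst functional results in both arms, and the direction of any bias is uncertain.

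**What to change.** Reword Completion Criteria and Withdrawal so that non-use, device failure and later loss of eligibility are recorded as events but do not end study follow-up. Whether such a patient continues with the app is for the sponsor to decide and need not be settled by this change. Let outcome collection end only with withdrawal of consent, death, or failed contact after documented attempts. State that all randomised patients are analysed in their assigned group with all available outcomes. Use the app-access record already planned under Limitations for a supportive analysis of app use, labelled as such.

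The change should be made before follow-up begins, because missed outcomes cannot be restored later. It costs a wording change, contact with non-users at visits already planned, and a diluted effect. With 83 analysed per group, power falls below 80% from about 20% non-use if non-users gain nothing. For 90% power, 90, 114 or 148 evaluable patients per group would be needed at 10, 20 or 30% non-use.

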#### Sample Size

The HL will be selected as the main outcome to evaluate the effectiveness. This outcome will be measured using the Spanish version of the 47-Item European Health Literacy Questionnaire (HLS-EU-Q47), which achieved a mean score of 32.88, over a possible range of 0 to 50 points, with an SD of 6.10 in the study setting [36]. An increase of at least 10% in the score will be considered clinically relevant due to the mHealth intervention. Accepting an α risk of .05 and a β risk of .90 in a bilateral contrast, 118 participants were needed in every group. A loss to follow-up rate of 30% was considered. However, the calculation is based on a minimum reference of sample observations, so an effort will be made to recruit as many participants as possible to increase the precision of the estimates.

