**Of main response**				
	Health literacy	0/50	HLS-EU-Q47^a^ [36]	Registration
		1-5/indicator	NOC^b^ code: 2015 [29]	Nursing record
	Self-management	1-5/indicator	NOC codes: 3102; 1803; 1830 [9,40]	Nursing record
		12-60	European Heart Failure Self-Care Behavior Scale [41]	Nursing record
	Number of readmissions 1m;12m	0-99	Registration	Registration medical history

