### Limitations

This study has some limitations that should be acknowledged. The lack of adequate mobile devices or the sensory or cognitive deficits of the target population is taken into account. Likewise, their digital illiteracy could be another limitation. Therefore, and being aware of the population group, digital training is contemplated. As for cognitive impairment, the usual caregiver is included in the intervention.

When evaluating the effectiveness of the intervention, we can find the influence of the variable “time of use of the app” (a record of access to the app will be obtained and monitored).

Finally, we must be aware of the possible loss of participants due to their clinical characteristics. Therefore, when determining the sample size, a loss rate of 30% has been taken into account. The aim is to obtain as many participants as possible to increase the precision of the estimates.

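### Loss of contact is a withdrawal criterion, although readmissions, a main response, come from the medical history and could still be recorded

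*Protocol article*

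**What the plan says.** Under Completion Criteria and Withdrawal, completion is tied to one visit: "A patient will be considered to have completed the study when he/she completes the postintervention evaluation". A list then follows, introduced by "The criteria for withdrawal of a participant will be", and its last item is "inability to contact for follow-up". The same list contains withdrawal of consent, and the text does not distinguish the consequences of the two.

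Table 3, in the block for the main response, includes "Number of readmissions 1m;12m". Its data source is given as "Registration medical history". The Sample Size section names a different outcome for the power calculation: "The HL will be selected as the main outcome to evaluate the effectiveness". That outcome is a questionnaire score.

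The Sample Size and Limitations sections both allow for a 30% loss. Limitations gives the reason: "we must be aware of the possible loss of participants due to their clinical characteristics".

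The article does not say whether records are still consulted after a withdrawal. It also does not say which patients enter the readmission analysis.

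**The concern.** Two kinds of follow-up are treated as one. A questionnaire or a consultation needs the patient; a count of admissions from the medical history does not. A rule that withdraws the whole participant when contact fails is wider than the readmission outcome requires, and it puts an unreachable patient on the same footing as one who has revoked consent.

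Readmission is not a minor outcome here. The abstract's conclusions and the Discussion both expect the app to reduce admissions. If patients become unreachable partly because they are ill, and the article itself links losses to clinical characteristics, then the patients removed may differ in exactly the quantity being counted. Readmissions would then be counted mainly in patients who stayed reachable, and randomisation would no longer protect the comparison. For this outcome, unlike the questionnaires, that loss can be avoided.

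**Working it through.** **Inputs, all from the protocol article**
- 118 participants per group and 30% loss (Sample Size).
- Mean 32.88, SD 6.10, relevant increase 10%, two-sided α of 0.05 (Sample Size). The stated β of 0.90 is read here as 90% power.
- 1:1 allocation (Randomization).
- Readmissions at 1 and 12 months from the medical history (Table 3).

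**Step 1. The plan's own figure.** The difference is 0.10 × 32.88 = 3.288. The usual formula for two means gives n = 2 × (1.960 + 1.282)² × 6.10² / 3.288² = 72.3, so 73 per group. With 30% loss, 73 / 0.70 = 104.3, so 105; the cruder 73 × 1.30 gives 95. The stated 118 is not reproduced. The present point does not rest on that figure, but the result means one cannot tell whether 118 already includes the allowance for losses. Step 2 therefore gives both readings.

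**Step 2. Upper limit on patients affected.**
- If 118 per group are recruited: 0.30 × 118 = 35.4, about 35 per arm. In total 0.30 × 236 = 70.8, about 71.
- If 118 per group must remain after losses: 118 / 0.70 = 168.6, so 169 per arm are recruited and 169 − 118 = 51 per arm are lost, 102 in total.

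Both figures treat every loss as failed contact. The article does not give that share, so the lower limit is 0.

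**Step 3. Outcomes set against the rule.**

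| Outcome | Needs contact? | Recordable after contact is lost? |
|---|---|---|
| Health literacy questionnaire | Yes | No |
| Other contact-based scales | Yes | No |
| Readmissions at 1 and 12 months | No, medical history | Yes, if consent covers it |

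Only the last row is lost unnecessarily. Access to records is already part of the study: under Assessment Eligibility, the participating professionals consult the digital history.

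**Step 4. Direction.** Suppose unreachable patients are sicker and the app merely keeps more of them in contact. More sick patients would then be counted in the app arm, and its recorded readmissions would look worse than control with no true difference. Suppose instead that the app improves health, and that reachability improves with it. The distortion could then hide a real benefit. The article gives neither admission rates by contact status nor contact rates by arm, so neither sign nor size can be computed.

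**The case against.** The strongest reply is that the article nowhere says record look-up stops at withdrawal, that admissions already recorded are deleted, or that withdrawn patients leave the readmission analysis. Nothing in Table 3 restricts the medical history to patients still in contact. What happens to data after withdrawal is commonly set out in the full protocol, the analysis plan or the consent form, none of which is shown. The sentence in Limitations concerns losses in general and does not mention failed contact; death or deterioration would fit it equally well. Health literacy, the sample-size outcome, is untouched.

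Much of this stands. A reader might infer that the plan collects no data after withdrawal and discards a main response. The documents do not support that: the loss follows from the ordinary meaning of withdrawing a participant, not from any statement. A reader might also infer that the readmission comparison is biased for or against the app by a calculable amount, and step 4 shows why it is not.

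The reply does not remove the point. The criterion is written down, and centres act on it during conduct. An analysis plan cannot recover admissions that nobody was told to extract.

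**Conclusion.** The point holds in limited form. The withdrawal rule does not separate loss of contact from the end of record-based follow-up, and so is broader than the readmission outcome needs. Followed in its ordinary sense, it would leave readmissions unrecorded in patients whose records are still available, and that missingness could be informative.

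Between 0 and about 35 patients per arm could be affected if 118 is the number recruited, or up to 51 per arm if 118 is the number to remain. The conclusion rests on three assumptions: that withdrawal carries its usual meaning, that the medical history captures admissions as Table 3 presumes, and that consent allows records to be used after contact is lost. It is confined to readmissions.

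**What to change.** In Completion Criteria and Withdrawal, replace the lost-contact criterion with wording such as: contact-based assessments missing; participant remains in the study. Add that readmissions are extracted from the medical history over the fixed 1- and 12-month windows, and analysed, for every randomised patient in both arms, unless the patient withdraws consent to use of records. Record the reason for lost contact by arm, so that any imbalance can be seen.

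The cost is a short change of text, a small amount of extra record look-up of a kind already done for other participants, and a check that the consent form covers use of records after contact is lost. The change should be made before follow-up ends, while centres can still be instructed.

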#### Sample Size

The HL will be selected as the main outcome to evaluate the effectiveness. This outcome will be measured using the Spanish version of the 47-Item European Health Literacy Questionnaire (HLS-EU-Q47), which achieved a mean score of 32.88, over a possible range of 0 to 50 points, with an SD of 6.10 in the study setting [36]. An increase of at least 10% in the score will be considered clinically relevant due to the mHealth intervention. Accepting an α risk of .05 and a β risk of .90 in a bilateral contrast, 118 participants were needed in every group. A loss to follow-up rate of 30% was considered. However, the calculation is based on a minimum reference of sample observations, so an effort will be made to recruit as many participants as possible to increase the precision of the estimates.

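### The sample-size statement gives a β risk of .90, which is 10% power, and 118 per group does not follow from the stated inputs even if 90% power was meant; power is nevertheless adequate

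*Protocol article*

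**What the plan says.** The sizing is in Methods, Sample Size. Health literacy is the outcome used: "The HL will be selected as the main outcome to evaluate the effectiveness". The instrument is the HLS-EU-Q47, and the article cites a reference result for it, "which achieved a mean score of 32.88, over a possible range of 0 to 50 points". The standard deviation that goes with that mean is given as 6.10. The target effect is relative: "An increase of at least 10% in the score will be considered clinically relevant due to the mHealth intervention". The error risks and the result share one sentence: "Accepting an α risk of .05 and a β risk of .90 in a bilateral contrast, 118 participants were needed in every group". The next sentence is "A loss to follow-up rate of 30% was considered". The section then treats the figure as a floor and says that more patients will be sought.

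The Limitations section returns to the loss: "when determining the sample size, a loss rate of 30% has been taken into account". The Randomization section fixes equal allocation within each centre. No size other than 118 per group appears anywhere. The article prints no number before allowance for loss and no formula for that allowance.

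**The concern.** The article prints every input that a two-group comparison of means needs, together with the result, so a reader should be able to get from one to the other. Two things prevent this.

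- **The error risk is wrong as written.** A type II risk of .90 means a 90% chance of missing the effect.
- **The obvious repair does not recover the number.** Reading .90 as the power still does not give 118, with or without the 30% loss.

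This section is the only basis the article gives for the trial's size and for the power of its main comparison. As printed, the stated risk, effect, SD and size cannot all be true together, and the power the trial really has is nowhere stated.

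**Working it through.** **Inputs** (Sample Size, except allocation)

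- Reference mean 32.88; SD 6.10.
- Difference: 10% of 32.88 = 3.288 points. Standardised: 3.288 / 6.10 = 0.539.
- α = .05, two-sided (z = 1.960).
- Allocation 1:1 (Randomization).
- Loss 30%.

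**Formula.** Evaluable patients per group: n = 2 (1.960 + z_power)² × SD² / Δ². Here SD² / Δ² = 37.21 / 10.811 = 3.442. Enrolled per group = n / (1 − 0.30).

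**Step 1: β = .90 as printed (power 10%, z = −1.282).** n = 2 × (0.678)² × 3.442 = 3.2, so about 4 per group, or 6 with the loss. The plan's 118 is not reproduced.

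**Step 2: β = .10 (power 90%, z = 1.282).** n = 2 × (3.242)² × 3.442 = 72.3, so 73 per group. The t test needs 73.3, so 74. Enrolled: 73 / 0.70 = 104.3, so 105; 74 / 0.70 = 105.7, so 106. The plan's 118 is not reproduced.

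**Step 3: other readings of the same text.**

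| Reading | Evaluable per group | Enrolled per group |
|---|---|---|
| 80% power | 55 | 79 |
| 90% power, one-sided | 59 | 85 |
| 90% power, Mann-Whitney (73 / 0.955) | 77 | 110 |
| 90% power, 10% taken of the 50-point range (5 points) | 32 | 46 |

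None gives 118.

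**Step 4: what 118 per group delivers on the stated effect and SD.** With 118 randomised and 30% lost, 118 × 0.70 = 82.6 are evaluable. The standardised test value is 0.539 / √(2 / 82.6) = 0.539 / 0.1556 = 3.46. Power = Φ(3.46 − 1.96) = Φ(1.50), or about 0.93; the t test with 83 per group gives 0.932. With no loss at all, 118 per group gives 0.985. The smallest difference detectable with 90% power at 82.6 per group is about 3.08 points, below the 3.288 aimed for.

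**The case against.** The strongest reply is that β .90 is plainly a slip for power .90, since nobody would take a trial of 118 per group to be sized for 10% power, and that the discrepancy errs on the safe side. Much of this stands. The slip is a small correction, and on the article's own effect and SD the planned size exceeds 90% power even after the full loss. A reader might infer from the mismatch that the trial is underpowered; step 4 shows that it is not. The reply does not deal with the second part, because correcting the label still leaves 105 to 106 where the article has 118.

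Two further inferences are tempting, and the document supports neither.

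- **That 118 is the evaluable number.** About 169 per group (118 / 0.70) would then have to be enrolled. The Sample Size wording alone is loose enough to allow this. But the Limitations section says "when determining the sample size, a loss rate of 30% has been taken into account", and 118 is the only size given, so the natural reading is that the loss is already inside it.
- **That the route to 118 can be identified.** A power of 95% with n multiplied by 1.3 comes close (90 × 1.3 = 117; 91 × 1.3 = 118.3). So does a difference of 3.1 points at 90% power (82 / 0.70 = 117.1, rounded up to 118), although 3.1 / 32.88 is 9.4%, below the stated 10%. Several unstated inputs land near 118 and the article points to none of them, so no particular mistake in the allowance for loss can be claimed.

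**Conclusion.** The point holds as a defect of reporting and reproducibility. The printed β is wrong, and 118 per group does not follow from the printed inputs: at 90% power they give 73 to 74 evaluable and 105 to 106 enrolled, so 118 is 12 to 13 more per group than the enrolled figure. Power is not at risk.

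This rests on four assumptions: the 10% is taken of the reference mean and applies as a between-group difference, the SD of 6.10 holds in both groups, the comparison is a plain two-sample test, and 118 is the number randomised, as the Limitations section implies. The correction should be made, but it does not call the trial's size into question.

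**What to change.** Keep 118 and rewrite the statement around it. In Sample Size:

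- Replace the β of .90 with the correct type II error.
- State the difference as 3.29 points with an SD of 6.10, two-sided α .05.
- State that 118 patients per group (236 in total) are to be randomised with the 30% loss included, leaving about 82 to 83 evaluable per group and about 93% power (β about .07). This agrees with the Limitations section.
- If 118 came from an input that the article does not give, such as another power, difference, SD or test, state that input so that the number can be reproduced.

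There is no need to lower the target to 106. The existing number is adequate, and 106 presumes a t test, whereas Data Analysis also allows the Mann-Whitney test (about 110 enrolled). The cost is wording only, with no added patients.
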